### Early Treatment Failure (ETF)

- Development of danger signs or severe malaria on days 0-3, in the presence of asexual parasitaemia,
- Parasite density on day 2 > day 0 count irrespective of axillary temperature,
- Presence of asexual parasitaemia on day 3 with fever (axillary temperature ≥ 37.5°C),
- Asexual parasitaemia on day 3 ≥ 25 % of count on day 0.

### Late treatment failure (LTF)

#### Late Clinical Failure (LCF)

- Development of danger signs or severe malaria after day 3 in the presence of parasitaemia,
- Presence of parasitaemia and fever on any day from day 4 to day 28, without previously meeting the criteria of ETF.

#### Late Parasitological Failure (LPF)

- Reappearance of asexual parasitaemia after initial clearance between day 4 and day 84 (identified as recrudescent infection by PCR analysis) in the absence of fever (axillary temperature <37.5°C) without previously meeting the criteria of ETF or LCF.

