## Outcome measures and sample size.

### End points

#### Primary end point

The primary end point will be the PCR-corrected adequate clinical and parasitological response (PCR corrected ACPR) at day 28.

ACPR is defined as the absence of parasitaemia on day 28 irrespective of the axillary temperature without previously meeting any of the criteria of early treatment failure or late clinical or parasitological failure.

Patients with late asexual parasite reappearance will be considered ACPR if the PCR analysis shows a new infection rather than a recrudescence.

The total treatment failure is defined according to the WHO criteria [25] as the sum of early and late treatment failures (for definitions see chapter 7.3 Treatment failure).

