### Per Protocol (PP) Population (or Evaluable Population)

Defined as all randomized patients who will be eligible according to the study protocol, received at least 80% of the study medication, will not take other anti-malarial drugs and, in case of the presence of asexual parasite stages on thick or thin blood smears, will have an evaluable PCR analysis.

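### Parasitaemia that persists after day 3 without fever can meet no failure definition, because late parasitological failure requires reappearance after clearance

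*Protocol*

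**What the plan says.** The protocol builds total failure from separate categories. Section 10.4.1.1 defines it "as the sum of early and late treatment failures".

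- **Early failure (11.3.1).** Two rules do not depend on fever: "Parasite density on day 2 > day 0 count irrespective of axillary temperature" and "Asexual parasitaemia on day 3 ≥ 25 % of count on day 0". A third needs parasites with fever on day 3. A fourth needs danger signs or severe malaria with parasites on days 0 to 3.
- **Late clinical failure (11.3.2.1).** Either danger signs or severe malaria with parasites after day 3, or "Presence of parasitaemia and fever on any day from day 4 to day 28, without previously meeting the criteria of ETF".
- **Late parasitological failure (11.3.2.2).** "Reappearance of asexual parasitaemia after initial clearance between day 4 and day 84", without fever and shown by PCR to be recrudescent.

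Success is defined separately. Section 10.4.1.1 says: "ACPR is defined as the absence of parasitaemia on day 28 irrespective of the axillary temperature without previously meeting any of the criteria" for early or late failure. Section 9.1 defines the cure ratio as the share of evaluable patients with this response (ACPR) at day 28.

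Section 12.2.2 limits the PP set to children who, among other conditions, "will not take other anti-malarial drugs" and have an evaluable PCR if a smear is positive. The evaluability text printed under 12.2.3 needs counts to day 28, or discontinuation for a PCR-confirmed recrudescent reappearance. Section 12.3.1 tests both success criteria in the PP population.

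**The concern.** Parasites that have never cleared cannot reappear, so the only late category open to a child without fever or danger signs excludes persistence by its own wording. Persistence after treatment is direct evidence of inadequate drug effect, and the protocol foresees that clearance may be slow: section 10.6 has children monitored daily until parasites and fever clear.

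At stake is the primary day 28 cure ratio. A child in this gap may be counted as a success, removed from the PP set, or left without a label, depending on the day 28 slide and on what the site does in the meantime. The trial is open label, so the classification should be fixed in advance and not left to local judgement.

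**Working it through.** **1. The one figure used from the plan.** Section 10.4.2 gives 235 evaluable patients per group. With 95% cure in both arms, a 5-point margin and 80% power, n = (z_alpha + z_beta)² × 2 × 0.95 × 0.05 / 0.05².
- One-sided alpha 0.05: (1.645 + 0.842)² × 38 = 235.
- The stated one-sided alpha 0.025: (1.960 + 0.842)² × 38 = 299.

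The stated 235 is therefore not reproduced at the stated alpha. That is a separate matter, and 235 serves here only as a denominator.

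**2. Which definitions apply.** Take an illustrative child with no fever or danger signs: 100,000/µL on day 0, a day 2 count not above that, 20,000/µL on day 3 and 5,000/µL on day 7.
- Early failure: the day 2 rule is not met. Day 3 is 20,000/100,000 = 20%, below 25%. There is no fever and no danger sign. Not met.
- Late clinical failure: no fever, danger sign or severe malaria. Not met.
- Late parasitological failure: no clearance, hence no reappearance. Not met.

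**3. What happens to this child.**
- *Negative on day 28, no other antimalarial:* meets the wording of ACPR and counts as cured. The child was never withdrawn, so the ITT rules do not correct this.
- *Another antimalarial before day 28:* section 11.3.3 provides rescue for early and late failures, and this child is neither. Section 12.2.2 excludes the child from the PP set. The evaluability text under 12.2.3 readmits a discontinued child only for recrudescent reappearance.
- *Positive on day 28, counts recorded and PCR evaluable:* not ACPR and not a defined failure. Under 9.1 the child is in the denominator and not in the numerator, so already a non-cure.

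**4. Size per child.** One child moved from failure to cure: 1/235 = 0.43 points. For exclusion, assume 12 other failures. As a failure the ratio is 222/235 = 94.47%. Excluded, it is 222/234 = 94.87%, a change of 0.40 points.

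**5. Illustration of leverage (assumed counts).** Suppose 235 per arm, 12 classified failures in each (223/235 = 94.9%), and k of the test-arm children otherwise cured belong to the gap. The protocol names no interval method, so a Wald limit is assumed: p1 − p2 − 1.96 × √[p1(1 − p1)/n1 + p2(1 − p2)/n2]. Lower limits in percentage points, where success needs more than −5:

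| k | counted as failures | excluded from PP | counted as cured |
|---|---|---|---|
| 0 | −3.98 | −3.98 | −3.98 |
| 1 | −4.48 | −4.01 | −3.98 |
| 2 | −4.98 | −4.04 | −3.98 |
| 3 | −5.48 | −4.07 | −3.98 |
| 5 | −6.47 | −4.13 | −3.98 |

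From k = 3 the handling decides the non-inferiority result in this example. This needs all such children to be in one arm. With three in each arm, all counted as failures, both ratios are 220/235 = 93.6%, and the limit is −1.96 × √(2 × 0.9362 × 0.0638/235) = −4.4, which still passes. The 90% criterion is met in every row.

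**The case against.** The strongest case on the other side has four parts.

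- **The group is small.** A reader might infer that any child without fever whose parasites never clear escapes the failure definitions. That is not so. The day 2 rule and the 25% rule in 11.3.1 work without fever, and danger signs or severe malaria with parasites count as failure before and after day 3. Only the remainder described above is uncovered.
- **A child still positive on day 28 is not counted as cured.** A reader might infer the opposite from the missing failure label. Sections 9.1 and 10.4.1.1 block it: ACPR requires a negative day 28 slide, and the ratio counts ACPR. The child would appear cured only if the ratio were computed as one minus the listed failures, which is not how 9.1 defines it.
- **The ITT analyses give partial protection.** Sections 11.2.2, 12.2.1 and 12.3.1 count a child withdrawn for another antimalarial as a failure. This stands for the withdrawal route, but the primary set is PP, and it does nothing for the child who is negative on day 28 and never withdrawn.
- **The routes need particular events.** Either a site leaves a parasitaemic child without further antimalarial treatment until the slides turn negative, or it treats the child without classing it as a failure. Both may be rare. Section 6 describes artemisinin combinations as giving fast responses, and nothing suggests a difference between arms.

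The first two parts set the limits of the point. The last two reduce its likely size. None of them closes the gap in the wording.

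**Conclusion.** The gap is real and follows from the protocol text alone. It covers a child without fever or danger signs, with a day 2 count not above day 0, a day 3 count positive but below 25% of day 0, and parasites persisting after day 3. Of the three outcomes, two can raise the PP cure ratio (negative on day 28, or removed after another antimalarial). The third, positive on day 28, leaves success and failure non-complementary without inflating the ratio.

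The size is about 0.43 points per child counted as cured and slightly less per child excluded. The total is unknown. A reader might assume that one or two per cent of one arm is affected and express that as a share of the margin, but the documents support neither that rate nor an imbalance between arms, and the number may be zero. The table shows only that a few children in one arm could matter if the result is close. It rests on assumed counts and an assumed interval method.

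**What to change.** For endpoint classification only, add a statement to 10.4.1.1 and 11.3.2.2 that makes ACPR and failure complementary:
- asexual parasitaemia persisting beyond day 3 without clearance is a non-cure in both the PCR-corrected and the uncorrected day 28 ratios, including when the day 28 slide is negative;
- the PCR recrudescence condition in 11.3.2.2 does not apply to it;
- such children stay in the PP set as failures.

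The statement should also say what clearance means. Section 10.4.1.2 uses two consecutive negative slides on different days for clearance time, but 11.3.2.2 does not refer to it. It should also say which slide after day 3 establishes persistence.

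Sections 10.4.1.1, 11.3.2.2, 11.3.3, 12.2.2 and the evaluability text under 12.2.3 must be reconciled with this, including whether these children fall under the rescue section. No clinical rule is proposed.

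The cost is a short amendment and a change to outcome coding on the CRF. Table 1 already schedules a smear at every visit. The downside is that cure ratios may become slightly less favourable.

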### Rescue Therapy

Atovaquone-proguanil (Malarone©; 20 and 8 mg/kg of body weight, respectively, administered once daily for 3 days) will be used as rescue treatment for both early and late treatment failures in both treatment arms with uncomplicated disease. Intravenous quinine and appropriate supportive care will be used for any cases that progress to severe malaria (requiring admission to the paediatric ward at Kilifi District Hospital).

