### Safety population

All subjects who have received any dose of the study medication will be included in the safety population. The analysis of the 28 and 63-day cure ratios will be performed both for the intention-to-treat (ITT) patient population (all randomised patients) and the evaluable patient population. Patients are evaluable for the analysis of the 28 and 63-day cure ratios if parasite counts are recorded up to Day 28 and 63 or the patient discontinues due to reappearance of *P. falciparum* confirmed by PCR genotyping to be recrudescent.

The ITT analysis also includes patients who discontinue before Days 28 and 63 due to other reasons. These patients will be counted in the ITT analysis as treatment failures regardless of their reason for discontinuation.

Safety and tolerability measurements will be summarised for the ITT patient population.

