## Statistical Analysis

### Primary end point analysis

The primary analysis will be based on a 97.5% (one-sided) confidence interval (CI) computed on the difference between the 28-day PCR corrected cure ratios (PP population) of the test and the reference treatments, respectively.

In order to claim that dihydroartemisinin-piperaquine is efficacious, the lower limit of the 97.5% confidence interval of the difference between the treatment groups must be >-0.05 and the point estimate for the 28-day PCR corrected cure ratio of dihydroartemisinin-piperaquine must be >0.90%, in the PP population.

All patients withdrawn from the study will be considered as failures in the ITT population (worst-case scenario).

For computing the PCR-corrected cure ratio, the following rules will be applied:

- The patients with reappearing asexual parasitaemia, which are subsequently found to be due to re-infections are considered as treatment success in both PP and ITT populations;
- The patients for whom the PCR analysis is not interpretable (or blood sample unavailable) are considered as treatment failure in the ITT population, but are excluded from the PP population.

Robustness of results for the primary end point will be investigated by using other analyses, such as the survival analysis techniques.

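### Rescue treatment depends on failure definitions that cannot be applied to an afebrile recurrence at the visit and that leave out uncomplicated febrile recurrences after day 28; the rules for re-infections before day 28 also conflict

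*Protocol*

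**What the plan says.** **Rescue.** Section 11.3.3 says atovaquone-proguanil "will be used as rescue treatment for both early and late treatment failures in both treatment arms with uncomplicated disease", and provides intravenous quinine for progression to severe malaria. Late failure is reached by three routes:

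- Section 11.3.2.1: danger signs or severe malaria with parasitaemia at any time after day 3.
- Section 11.3.2.1: "Presence of parasitaemia and fever on any day from day 4 to day 28, without previously meeting the criteria of ETF".
- Section 11.3.2.2: reappearance of asexual parasites between day 4 and day 84, "identified as recrudescent infection by PCR analysis) in the absence of fever".

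**Re-infections.** Section 10.4.1.1 states: "Patients with late asexual parasite reappearance will be considered ACPR if the PCR analysis shows a new infection rather than a recrudescence". Section 12.3.1 says of recurrences "which are subsequently found to be due to re-infections are considered as treatment success in both PP and ITT populations".

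**Withdrawals.** Section 10.8.2, item 1, makes any treatment failure a reason for withdrawal. Section 12.3.1 adds: "All patients withdrawn from the study will be considered as failures in the ITT population (worst-case scenario". Section 12.2.1 counts every withdrawal except loss to follow-up as a failure. Section 12.2.3 keeps a child who stops early evaluable only if the recurrence is "confirmed by PCR genotyping to be recrudescent". Of those who stop early for other reasons it says: "These patients will be counted in the ITT analysis as treatment failures regardless of their reason for discontinuation".

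**The concern.** There are two separate problems.

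The first is clinical. The patients are children aged 6 to 59 months, followed for 84 days, and recurrences are expected: section 10.5.5 estimates about 50 breakthrough infections. A rescue rule has to work with what staff know on the day, namely smear, temperature and clinical signs. Here it turns on a PCR result for one group and names no trigger for another. The same definitions feed the later cure ratios, so the second gap is also an end-point defect.

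The second is analytic. The day-28 PCR-corrected ITT ratio depends on which section the analyst follows for a child with a re-infection who stopped early. Section 12.3.1 labels the ITT analysis a worst case, and readers will use it to judge whether the per-protocol result is robust.

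**Working it through.** **Step 1. Which recurrences trigger rescue?** Applying sections 11.3.2.1 and 11.3.2.2 as written to children without danger signs or severe malaria:

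| Recurrence | PCR recrudescent | PCR re-infection | PCR unclassifiable |
|---|---|---|---|
| Days 4-28, febrile | late clinical failure | late clinical failure | late clinical failure |
| Days 4-28, afebrile | late parasitological failure | no class | no class |
| Days 29-84, febrile | no class | no class | no class |
| Days 29-84, afebrile | late parasitological failure | no class | no class |

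- In the afebrile rows the class depends on PCR. Section 10.5.3 describes dried filter papers that are stored, dispatched and compared with the day-0 sample, and section 12.3.1 speaks of re-infection being found subsequently. The result is not available at the visit.
- The febrile row after day 28 is empty whatever the PCR result. Section 10.4.1.2 nevertheless lists cure ratios for days 42, 63 and 84.
- No other section names a drug for the empty cells. The recurrent-parasitaemia column of Table 1 lists assessments only.

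**Step 2. How is a febrile re-infection on days 4-28 counted?**

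- Failure: section 11.3.2.1 has no PCR condition, so it is a late clinical failure. Section 10.8.2 item 1 withdraws the child. Sections 12.2.1 and 12.3.1 count the withdrawal as an ITT failure, as does section 12.2.3 for a stop before day 28.
- Success: sections 10.4.1.1 and 12.3.1.
- Evaluability: section 12.2.3 leaves a re-infection that stops before day 28 outside the evaluable set, while section 12.3.1 counts it as a per-protocol success.

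No order of precedence is written.

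**Step 3. Size in the ITT analysis.** Input: 250 per arm (section 10.4.2).

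- Per child: 1/250 = 0.4 points in that arm.
- Imbalance equal to the 5-point margin: 0.05 × 250 = 12.5 children.

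The protocol does not give re-infection counts before day 28, so the direction can only be shown on assumed counts. Start from 238/250 (95.2%) in both arms. The lower limit is d − 1.96 × √[p₁(1−p₁)/n₁ + p₂(1−p₂)/n₂], with d the test minus reference difference. Then recode re-infections as failures:

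| Recoded, test / reference | Cure ratios | Difference | Lower limit |
|---|---|---|---|
| 0 / 0 | 95.2% / 95.2% | 0.0 | −3.7 points |
| 10 / 10 | 91.2% / 91.2% | 0.0 | −5.0 points |
| 5 / 15 | 93.2% / 89.2% | +4.0 | −1.0 points |
| 15 / 5 | 89.2% / 93.2% | −4.0 | −9.0 points |

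Equal counts make ITT stricter. An excess on the reference drug makes it more lenient, and an excess on the test drug makes it harsher.

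**Step 4. Size in the per-protocol analysis.** Input: 235 per arm (section 10.4.2). Assume 223/235 = 94.9% in both arms, which gives a lower limit of −4.0 points. If section 12.2.3 is followed and re-infected successes are dropped:

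- 10 per arm: 213/225 = 94.7% in both arms, lower limit −4.2 points.
- 5 test, 15 reference: 218/230 = 94.8% v 208/220 = 94.5%, difference +0.2, lower limit −3.9 points.
- 15 test, 5 reference: difference −0.2, lower limit −4.4 points.

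All stay inside the margin.

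**The case against.** **The ITT rules can be reconciled.** Section 12.3.1 gives a general rule for withdrawals and then a specific one for the PCR-corrected ratio. Ordinarily the specific rule governs, and section 10.4.1.1 agrees with it. Section 12.2.1 justifies counting withdrawals as failures by a possible link with lack of efficacy, which a confirmed re-infection does not show. This stands: success is the more natural reading. But no precedence is written, and sections 12.2.1 and 12.2.3 make no exception for re-infections, so a clarifying sentence is still needed.

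**The decision rests on the per-protocol population.** This also stands, and step 4 shows little movement.

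**Late febrile recrudescences are partly covered for analysis.** Section 12.2.3 keeps a PCR-confirmed recrudescence evaluable to day 63 whether or not there was fever. That helps an analyst, but it supplies neither a failure class nor a rescue trigger.

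**Clinicians would treat these children anyway.** Probably so. A reader might infer that the protocol withholds treatment, but it does not. Section 10.6 has children seen on request to day 84, danger signs or severe malaria after day 3 are a failure at any time, and severe cases receive quinine. The defect is an unstated trigger and drug.

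**A stronger reading of the afebrile case.** A reader might infer that treating an afebrile re-infection counts as antimalarial use outside the protocol (section 10.8.2 item 3, section 11.2.2) and so as an ITT failure. That assumes treatment given by study staff for a recurrence found in the study is off-protocol. Read that literally, section 11.2.2 would also catch the rescue drug itself. Only the febrile route in step 2 follows directly from the text.

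**Conclusion.** The point holds as a drafting defect with a clinical side, and it should be corrected. The rescue trigger cannot be applied at the visit to afebrile recurrences and is absent for uncomplicated febrile recurrences on days 29-84. The latter also fall outside every failure class for the later cure ratios. The rules for a febrile re-infection on days 4-28 conflict in ITT, and section 12.2.3 conflicts with section 12.3.1 on whether a re-infection that stops early is evaluable.

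The effect is 0.4 points per affected child in its arm's ITT ratio, assuming the 250 per arm of section 10.4.2. The number of affected children cannot be derived, because the roughly 50 breakthrough infections are not split by day, fever or PCR class.

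A reader might infer that the ITT analysis is biased towards non-inferiority, since the protocol sets out to estimate a chemoprophylactic effect of dihydroartemisinin-piperaquine. The documents do not support that as a finding. They give no re-infection counts by arm before day 28, and with equal counts the recoding makes ITT stricter. Nor do they support a claim that the primary conclusion is at risk.

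**What to change.** - **Section 11.3.3:** give the protocol rescue drug for any recurrent asexual parasitaemia on days 4-84, regardless of fever or PCR result, after the genotyping sample is taken. The word asexual matters because gametocyte carriage is followed separately.
- **Section 11.3.2.1:** extend the fever criterion to day 84, with re-infections reclassified by PCR for the PCR-corrected ratios. Without that condition, late febrile re-infections would become failures and the conflict would grow.
- **Sections 10.8.2, 12.2 and 12.3.1:** state that protocol rescue is not prohibited antimalarial use. State also that a PCR-confirmed re-infection stays evaluable and counts as a success in the PCR-corrected per-protocol and ITT analyses, identically in both arms, overriding the withdrawal rule.

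The cost is an amendment of a few sentences and possibly a few more rescue courses. No visit or test is added: Table 1 already has the smear and the genotyping sample at recurrence.

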# DATA MANAGEMENT

## Data Recording

A case-record form (CRF) will be completed for each patient documenting demographic and anthropometric data, symptoms prior to clinic attendance, concomitant illness, drug history, results of physical examinations, vital signs, laboratory results incl. parasitology, haematology and clinical chemistry, and study drug administration. All entries will only be made by authorized study team members and dated and initialized. CRFs will be kept in a secure area to ensure confidentiality of medical and personal data.

